|                                 |                                                                                                                                                                                                                                                                                                                                                                                                                                                                                                                                                                             |
|---------------------------------|-----------------------------------------------------------------------------------------------------------------------------------------------------------------------------------------------------------------------------------------------------------------------------------------------------------------------------------------------------------------------------------------------------------------------------------------------------------------------------------------------------------------------------------------------------------------------------|
|                                 | 
 
• Participation in a clinical trial in the last month
 
• Unable to commit to the appointment schedule or perform the tasks required in the study.
 
                                                                                                                                                                                                                                                                                                                                                                 |
| Study Intervention:             | Participants will be randomised to one of four groups. Each Participant will be enrolled in the lifestyle programme. The initial six months will be focused on weight loss. The weight loss diet (total fat intake of < 30% and saturated fat < 10% of total energy) will be hypo-caloric with a 500 kilocalorie deficit (based on the Harris Benedict Equation for estimating energy requirements). All Participants will continue to be followed up by onsite assessments at months 9 and 12 and will be randomised to a weight loss maintenance intervention at month 6. |
| Safety Parameters:              | Adverse Event and Serious Adverse Event monitoring.                                                                                                                                                                                                                                                                                                                                                                                                                                                                                                                         |
| Laboratory Parameters/Analysis: | TSH, Creatinine, eGFR, FBC, Fasting glucose, HbA1c, Full lipid profile, Liver enzymes, hsCRP, Apolipoprotein B, plasma SCFA, faecal SCFA, and microbiota community 16s rDNA profile.                                                                                                                                                                                                                                                                                                                                                                                        |
| Total Blood Volume:             | ~ 50 ml of blood                                                                                                                                                                                                                                                                                                                                                                                                                                                                                                                                                            |
| Sample Size Determination:      | The study is powered for the smallest difference between two of the groups for each outcome, with the larger sample size being adopted.                                                                                                                                                                                                                                                                                                                                                                                                                                     |
| Statistical Analyses:           | Data will be analysed for normality using the Shapiro-Wilk test. For analysis of differences between treatments, an analysis of co-variance (ANCOVA), or the non-parametric equivalent will be used. For within group changes, repeated measures ANOVA will be used. As well as an analysis of completers (those that attend the final visit), an intention to treat (ITT) analysis will also be included. For the ITT analysis, dropouts will be treated using a variety of sensitivity analyses.                                                                          |

## 2 Introduction

Type 2 diabetes mellitus is the fastest growing chronic illness in Australia, and over 3.2 million people are estimated to have pre-diabetes and diabetes, with a further 275 individuals being diagnosed with diabetes every day. As diabetes is the 6th leading cause of death in Australia, interventions to prevent this condition and its complications are a priority for Australian society.

### Alpha-Cyclodextrin

Dietary fibres have long been known to bind to dietary fat; typically on a 1:1 or perhaps as high as a 1:1.4 ratio. Such small ratios make the common dietary fibres impractical as an aid for weight loss and would require the individual to ingest very large amounts of fibre to remove a significant amount of dietary fat and this is not practical. Therefore, there is importance in finding a more efficient fat binder. One such example is FBCx (a formula based on  $\alpha$ -cyclodextrin ( $\alpha$ -CD)), a polysaccharide, derived from corn, of six glucose units that are covalently attached end to end via  $\alpha$ -1, 4 linkages. Artiss and colleagues (2006) demonstrated that  $\alpha$ -CD could bind triglyceride and at ratios that are significantly different from the 1:1 that is typical for dietary fibres. This animal study demonstrated that  $\alpha$ -CD has the unique ability to complex with and prevent the absorption of 9 times its own weight in dietary fat. It appears that  $\alpha$ -CD forms a very stable complex or emulsion with the dietary fat in the stomach and remains bound to the fat through the gastro-intestinal (GI) tract, first preventing the absorption of the bound fat in the small intestine and then fermentation by the intestinal flora.

Previous research examining the effect of  $\alpha$ -CD on weight loss has shown that is effective in reducing and/or maintaining body weight in obese patients with type 2 diabetes, without the need for reduced energy intake or an increased exercise programme (Grunberger, 2007). In this study both cholesterol and triglyceride levels were reduced in those who had hyper-triglyceridaemia (Grunberger, 2007). There was no change in high density lipoprotein (HDL) cholesterol levels. Furthermore, significantly elevated adiponectin levels indicated an increase in insulin sensitivity which might delay the onset of usage of insulin and/or reduce the amount of supplemental insulin required in these participants (Grunberger, 2007). Another study has also shown reduced atherogenic lipoproteins (apolipoprotein-B) with the supplementation of  $\alpha$ -CD in healthy overweight individuals (Comerford, 2011).

Supplementation of  $\alpha$ -CD potentially alters the activities and growth of certain microbiota in the gut, such as known cyclodextrin utilizer *B. thetaiotaomicron*. Following oral administration,  $\alpha$ -CD is fermented by intestinal microbiota to short chain fatty acids (mainly acetate, propionate, and butyrate) prior entering the circulation (Van Ommen, 2004).

Hydrolysis by gut microbiota may lessen the fat-binding benefits of  $\alpha$ -CD and therefore may alter its efficacy in promoting weight loss.

### Compound K

The root of ginseng has been used for remedies in traditional Chinese medicine, most recently for improving glycaemic control. The pharmacological properties of ginseng are mainly attributed to the ginsenosides, the active components found in the extracts of different species of ginseng (Attele, 1999). Numerous studies have been conducted and found that these have anti-diabetic properties (Yokozawa, 1985; Attele, 2002; Vuksan, 2005). Ginst15 (a ginseng extract formula based on Compound K) (CK), which is a final metabolite of protopanaxadiol ginsenosides following a hydrolysis by intestinal microbiota (Akao, 1998; Tawab, 2003), has been shown to be the active ingredient for this anti-diabetic action. CK enhances insulin secretion by acting directly on the pancreas (presumably). Significant improvements have been shown in both plasma glucose and insulin levels in diabetic *db/db* mice when treated with CK and metformin combination therapy versus metformin therapy alone (Yoon, 2007).

As an adjunct to the trial with respect to the current treatment for overweight and obesity, blood (to measure gut hormones and adipokines) and stool samples (to measure gut microbiota) will be collected at specified time points. It has been shown that energy restricted diets have a negative effect on the circulating mediators of appetite, which encourages weight regain (Sumithran, 2011) and therefore long-term strategies to counteract this change are needed to prevent obesity relapse. Furthermore, with the advances in molecular biology techniques, the association between changes in the gut microbiota with diet and human diseases or disorders is becoming more evident. Of particular relevance to this study, the composition of the colonic microbiota and the balance of its metabolic products are strongly influenced by degree of weight loss, by diet, and in particular, by the intake of resistant carbohydrates and dietary fibre (Scott, 2008).

Based upon these properties of  $\alpha$ -CD and CK, the current double blinded, randomised controlled trial is designed to investigate the beneficial effects of these products in overweight and obese participants with pre diabetes. It is proposed that these products may over-lap in their function and therefore are being compared in the same trial in the prevention of type 2 diabetes.

### Weight loss goals

There is a debate in the literature regarding the impact of goals on participants' weight loss in behavioural weight loss treatments (Stubbs, 2011; Linde, 2004; Foster, 1997; Foster, 2004; Wadden, 2004). One perspective postulates that unrealistic, high goals are

detrimental to weight loss. On the contrary, some researchers have suggested that larger goals may actually stimulate larger weight losses. This perspective is based on empirical research reporting a positive linear relationship between goals and performance outcomes (Locke, 1990; Locke, 2002). At present, the evidence is inconsistent regarding the relationship between goals and weight loss in overweight and obese individuals participating in treatment. Given these discrepancies, it is plausible that other psychological processes are involved in this relationship. Goal-Setting Theory (Locke, 1990, Locke, 2002) acknowledges that although high goals may be related to superior performance outcomes, there are other important factors in this relationship including an individual level of self-efficacy, outcome-expectancies and commitment to achieving that goal. To date, previous research has been compromised by the common failure to address the moderating impact of these important constructs within the relationship between goals and weight loss.

The theoretical relationship between effort, dissatisfaction, negative behavioural consequences and goal abandonment has also not been carefully investigated in a weight loss context. Most participants in weight loss treatments aim to lose more weight than is characteristic of those interventions and as a result, in general, participants do not meet their goals (Foster, 1997; Foster, 2004; Jeffrey, 1998; Wadden, 2003). Research in the broader psychological literature has demonstrated that the pursuit of unattainable goals can lead to negative behavioural consequences including goal abandonment and depressive focusing style (Carver, 1990; Cervone, 1993; Higgins, 1987). Further research is needed to better understand these relationships.

The aim of this sub-study is two-fold: To test goal-setting theory within a weight loss context and then to better understand the relationship between unmet goals, dissatisfaction and negative behavioural consequences.

#### Weight loss maintenance

Although there are successful interventions that help people to lose weight many people regain the weight they have lost and thus weight maintenance remains a critical challenge. The period after initial weight loss is when people are at highest risk of weight gain. Few people (1 in 10) recover from even minor lapses of 1-2 kg of regain in weight (Wing, 2006) Therefore preventing small regains from turning into larger relapses appears critical for weight loss maintenance.

A systematic review of randomised controlled trials of weight loss maintenance interventions for obese adults identified that the greatest need for further research was in the area of lifestyle interventions focused on supporting people to manage their weight in the longer term by regulating food intake and increasing physical activity (Dombrowski, 2014). There were four important features of effective weight maintenance interventions,

all of which are consistent with self-regulation theory; these being goal setting, self-monitoring of weight and behaviour, action plans for weight control through dietary and physical activity behaviours and plans on how to cope with risk factors for weight regain and relapse prevention.

### Self-weighing and accountability

The potential efficacy of self-weighing is based on the principles of self-regulation theory. Self-regulation has been described as a process that has three distinct stages; self-monitoring, self-evaluation and self-reinforcement. The awareness fostered during self-monitoring is considered an essential initial step in promoting and sustaining behaviour change. Self-monitoring in the context of self-weighing can show individuals how their behaviour affects their weight and allows them to adjust their behaviour to achieve their goals. It is simple for a health professional or public health communication to advocate and it is simple for people to understand and implement. It is the kind of behaviour that could become habitual. Trials have shown that participants can adhere to daily self-weighing (Steinberg, 2013). Presently one trial in the UK is investigating the effectiveness of self-weighing for weight loss maintenance (Madigan, 2015). Participants in the intervention group are asked to weigh themselves daily and record their weight. They are also sent generic reminder text messages and receive three phone calls to encourage self-weighing (Madigan, 2015). The participants are given scales that send the weight through a cellular system to a database in real time. In this trial the scales are being used as an objective measure of self-weighing and the participants are told their weights will not be checked. That said, participants often report feeling pleased that someone will be watching their weight and perceive they are accountable to someone. This sense of accountability may help people to stay on track with their weight maintenance or it may act in combination with self-weighing as an effective strategy. A systematic review of self-weighing for weight loss found that in sub group analyses, trials with accountability had greater weight loss (Madigan, 2015). However no trial has directly assessed this.

No previous study has collected data about how people use the reading on the scale as a tool to change their physical activity or dietary behaviours. In a small subgroup of participants this will be examined by collecting data about their thoughts and behaviours when they step on the scales and reflect on their weight.

The aim of this sub-study is to evaluate the effectiveness of the concept of accountability on weight regain six months after completing a weight loss programme and to examine the behavioural strategies used in combination with self-weighing.

## Effect of weight-loss and maintenance programmes on change in patterns of thought

Both our weight-loss and maintenance programmes are likely to change the way our patients think about themselves and their environment. Patterns of thought - embodied in personality traits and preferences - have been linked frequently to healthy behaviours and obesity (e.g. Cobb-Clark, 2014; Kern, 2009; Courtemanche, 2014; Ikeda, 2010; Smith, 2005; Yamada, 2013). The literature is still divided on whether such patterns of thought are fixed in adulthood and whether interventions can change them (Cobb-Clark, 2012, 2013; Schurer, 2015; Tymula, 2013).

In this sub-study we assess whether the programmes are successful in changing otherwise stable patterns of thought and beliefs, whether the success of these programmes depends on (a) the initial level of patterns of thought of a patient, or (b) the patient's ability to change his or her patterns of thought as the intervention proceeds.

Knowledge of the magnitude of change in patterns of thought can allow us to calculate the wider economic benefits of our intervention programmes in terms of gained hours in the labour market and reduced health care costs. This can be done by calculating by how many standard deviations measured patterns of thought - derived from standard instruments such as the Five Factor Model and risk and time preferences- increase or decrease, and then using this empirically derived magnitude of change to calculate the gains in productivity due to a change in these patterns of thought provided in previous studies (See Cobb-Clark, 2012; 2013). For instance, if our weight maintenance intervention increases self-efficacy - one of many proxies of patterns of thought - by 1 standard deviation, then we know from the previous literature that such a change implies a 0.1 standard deviation increase in hourly wages in the Australian context (See Cobb-Clark, 2011).

To be able to most objectively measure these patterns of thought, we collect data on Five Factor Model (Conscientiousness, Openness to Experience, Agreeableness, Extraversion, Neuroticism) and questions about the personality of hypothetical persons to control for scaling bias in self-assessments. These were developed by [name] and [name] adapted from Bolt et al. (2014) for the purpose of a student survey that is currently underway at the University of Sydney (See [www.sydney.edu.au/economics/survey](http://www.sydney.edu.au/economics/survey)). To control for gender biases in the evaluation of hypothetical persons, we randomly assign female and male gender to each of the three vignettes a patient is asked to evaluate. We will also collect task-based measures of risk and time preferences. We propose to use standard tasks from economics developed by Holt & Laury (2002) and Andreoni & Sprenger (2012) to measure risk and time preferences in obese participants to verify whether the intervention affects these decision-making fundamentals that have been previously identified to correlate with being overweight.

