#### Secondary Objectives

1. The effect of each product and the combination of products absolute on weight loss (kg) and percentage of weight loss, relative to baseline body weight.
2. To examine the changes in full lipid profile (including total cholesterol, high-density lipoprotein (HDL), low-density lipoprotein (LDL)), apolipoprotein B, plasma glucose, and glycated haemoglobin (HbA1c) between groups.
3. To compare the percentage of Participants in each category of glucose tolerance (normal, impaired fasting glucose, and type 2 diabetes) between groups at study completion.
4. To examine changes in body composition by waist circumference, fat mass, fat free mass, and blood pressure between groups.
5. To examine the changes in other biochemical parameters (liver enzymes and inflammatory markers) between groups.
6. To measure the side effect profile of each product using adverse event (AE) reporting.
7. To investigate the change in vitality between groups using the vitality scale of the short form (SF) SF-36 Health Survey.
8. To investigate the relationship between goals, outcome-expectancies, self-efficacy, commitment and weight change across all groups
9. To investigate the relationship between unmet goals, effort, dissatisfaction and weight change across all groups.
10. To investigate the effect of the intervention type on changes in personality (Five Factor Model, self-efficacy) and preferences (risk and time).
11. To investigate whether efficacy of the intervention type depends on the change in personality/preferences.
12. To determine the cost-effectiveness of each intervention relative to the lifestyle programme alone by measuring the cost per quality adjusted life year (QALY).

13. To determine whether weight loss results in better financial outcomes for Participants
14. To measure the change in gut hormones and adipokines between groups.
15. To investigate the long-term outcome of the gut microbiota profile between all groups.
16. To compare the metabolic activity of gut microbiota between groups (short chain fatty acids (SCFA) production in plasma and faeces).
17. To investigate the dynamics of the microbiota community as a result of dietary supplementation and elimination of FBCx and Ginst15 across all groups.
18. To determine the difference in handgrip strength throughout the study.

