19. To determine circulating hormones or factors that influence muscle mass or strength, such as but not limited to insulin like growth-factor 1 (IGF-1), IGF-1 binding proteins and cortisol.
20. To evaluate the efficacy of three follow up programmes in preventing weight regain after a weight loss phase.
21. To identify the behavioural strategies people use and the psychological processes that enable them to adopt weight management behaviours (prompted by regular self-weighing).
22. To determine whether practitioners' intuition predicts weight loss.
23. To measure the change in cognitive function between groups and by weight loss achieved (0±1%, 5-10%, >10% weight loss).
24. To identify if a change in diet modifies the oral health in obese people.

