**7.5 Randomisation**

All treatment groups will include a standard behavioural management programme (nutrition, exercise, and behavioural advice for weight loss) and be allocated to one of four treatment groups (FBCx; Ginst15; FBCx + Ginst15 combined; or placebo using a randomisation programme (FileMaker Pro).

Randomisation will be based on a simple block randomisation.

The Investigators (except for the data manager (Associate [name]), Participants and Sponsor will be blinded as to their treatment allocation. All containers will look identical between the groups other than the additional information of A, B, C or D.

At the commencement of the weight loss maintenance period (month 6), Participants will be randomised to one of three follow-up weight maintenance groups. Random group allocation will be by initial intervention arm and stratified by weight loss during Baseline to 6 months.

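### Change in personality and preferences over the weight-loss phase has no comparator, so it cannot show that programme's success or its economic benefit

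*Protocol*

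**What the plan says.** The Introduction, under the heading on the effect of the programmes on patterns of thought, starts from the expectation that "Both our weight-loss and maintenance programmes are likely to change the way our patients think" about themselves and their surroundings. The sub-study's aim is given as "we assess whether the programmes are successful in changing otherwise stable patterns of thought and beliefs". The economic step follows: "Knowledge of the magnitude of change in patterns of thought can allow us to calculate the wider economic benefits of our intervention programmes". The method begins "This can be done by calculating by how many standard deviations measured patterns of thought - derived from standard instruments", goes up or down, and then applies productivity effects from earlier studies to that magnitude. The worked example supposes that the maintenance intervention raises self-efficacy by 1 SD and states that "such a change implies a 0.1 standard deviation increase in hourly wages in the Australian context". No comparator is named in any of these sentences.

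Section 7.5 states: "All treatment groups will include a standard behavioural management programme". The Synopsis (Study Intervention) likewise enrols every participant in the lifestyle programme. Sections 6.3.10 to 6.3.12 schedule the self-efficacy, personality and preference instruments at Baseline, Month 6 and Month 12. Section 6.2.7 randomises participants at Month 6 to usual care, self-weighing, or self-weighing plus accountability.

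**The concern.** The text credits two programmes, and the design treats them differently. The maintenance groups are randomised against usual care. The weight-loss programme is common background to all four product arms, and the whole span from Baseline to Month 6 lies inside it.

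Scores on such instruments can move without any programme effect. Time passes, people answer the same items again, and people who enrol at an untypical moment drift back towards their usual level. The sign is not known in advance: a downward drift would hide a benefit just as an upward one would create it. If the stated calculation is followed for the weight-loss programme, whatever moved everyone is reported as that programme's success and given a wage value. That is a causal and monetary claim which the design cannot support.

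**Working it through.** **Inputs**
- Wage factor: 0.1 SD of hourly wages per 1 SD of self-efficacy (Introduction, patterns-of-thought heading).
- Participants: 400, with 15% drop-out at 6 months (Section 11.3), so 400 × 0.85 = 340 at Month 6, or about 340 / 3 ≈ 113 per maintenance group.
- Common drift δ (in SD units) and the pre/post correlation ρ are not in the protocol. Both are assumed below, with ρ from 0.5 to 0.8.

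**The protocol's own figure.** The 0.1 factor comes from a cited outside study and cannot be rederived from the protocol. It is taken as given.

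**What each comparison estimates.** Let τ be the effect of the weight-loss programme, π the effect of a product arm, and δ the drift shared by everyone.
- Change from Baseline to Month 6 in one arm: τ + π + δ.
- Difference between two product arms: (τ + π₁ + δ) − (τ + π₀ + δ) = π₁ − π₀. Drift cancels, but so does τ.

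No combination of the four arms contains τ without δ, so the weight-loss programme's effect is not identified.

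For Month 6 to Month 12, let μ be the effect of a maintenance group and δ′ the drift over that period. Then (μ_g + δ′) − (μ_usual care + δ′) = μ_g − μ_usual care. Here drift cancels and the quantity of interest stays.

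**Wage value booked when the true effect is zero** = 0.1 × δ:

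| Assumed drift (SD) | Before-and-after result (SD of hourly wages) | Expected randomised contrast |
|---|---|---|
| 0.1 | 0.01 | 0 |
| 0.2 | 0.02 | 0 |
| 0.3 | 0.03 | 0 |
| 0.5 | 0.05 | 0 |

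**How readily such a drift would look real (illustration only).** Take a paired comparison at two-sided 5% with n = 340. The SD of change is √(2(1 − ρ)) and the standard error is that divided by √340. The probability of a significant result is Φ(δ/SE − 1.96) + Φ(−δ/SE − 1.96).
- ρ = 0.5: SE = 1/√340 = 0.054. At δ = 0.1 the probability is 0.45; at δ = 0.2 it is 0.96.
- ρ = 0.8: SE = √0.4/√340 = 0.034. At δ = 0.1 the probability is 0.83; at δ = 0.2 it is above 0.99.

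**What the valid maintenance contrast can detect.** With 113 per group, 80% power and two-sided 5%, a pairwise contrast of change scores detects (1.96 + 0.8416) × √(2(1 − ρ)) × √(2/113), which is 0.37 SD at ρ = 0.5 and 0.24 SD at ρ = 0.8. On the protocol's factor that is about 0.037 and 0.024 SD of hourly wages. Further loss between Month 6 and Month 12 would raise these values.

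**The case against.** The strongest reply is that this is background, not an analysis plan. The paragraph sits in the Introduction, its wording is permissive, and it names no test or time points. Secondary objective 10 asks for the effect of intervention type on personality and preferences, Section 11.4 provides ANCOVA for differences between treatments, and a statistical analysis plan may settle the estimator.

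Much of that stands, and it rules out several stronger readings.
- A reader might infer that the usual-care group is left out of the calculation. The text does not say so. Its only worked example concerns the maintenance intervention, the programme that does have a randomised usual-care group.
- A reader might see a contradiction with objective 10. The two are compatible: the objective implies a comparison that the paragraph leaves unstated.
- A reader might extend the point to secondary objective 24, "To identify if a change in diet modifies the oral health in obese people". The Introduction frames that hypothesis as an association, and diet diaries are collected (Section 6.3.16), so individual change in diet can be related to oral change. Only the causal verb is open to comment.
- The significance probabilities rest on an assumed drift, an assumed correlation and a paired test that the protocol does not name. They illustrate the mechanism and are not an error rate of the plan.

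The reply does not reach the weight-loss programme. The paragraph names it among the programmes to be judged and valued, and a choice of estimator cannot supply a comparator that the design lacks.

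**Conclusion.** The point holds for the weight-loss programme only. Its effect on patterns of thought, and hence its economic benefit, cannot be estimated from this trial, because every participant receives it. Any drift common to all participants would be valued as benefit, at 0.1 SD of hourly wages per SD of drift if the protocol's self-efficacy factor is used; the 0.2 SD example gives 0.02 SD. The conclusion about identification follows from the design alone. The sizes depend on an assumed drift for which the protocol offers no value.

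For maintenance, a valid randomised contrast exists, and the paragraph should say that it is the one to be used. The matter is confined to a secondary sub-study and does not touch the primary endpoints, the sample size or data collection. It still merits correction, because the output is a causal claim with a wage value attached.

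**What to change.** Amend the patterns-of-thought paragraph of the Introduction so that the wage or productivity conversion is applied only to differences between randomised groups, with their confidence intervals, in line with objective 10:
- Maintenance: Month 12 score in Groups 2 and 3 against usual care, adjusted for the Month 6 score.
- Products: Month 6 score by FBCx and by Ginst15, adjusted for the baseline score.

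Describe change from Baseline to Month 6 across all participants as descriptive and uncontrolled, and remove the claims that it shows the weight-loss programme's success or economic benefit.

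The cost is wording; the instruments and visits stay as they are. The scientific price is that no causal economic claim can be made for the weight-loss programme, and that the maintenance figure becomes the gain over usual care, estimated less precisely than a change pooled over all participants.
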